#### Efficacy: other study parameters

IIITime-to-recommended wheelchair utilization. For each individual, we will define an indicator variable whether the patient uses (or has a recommendation for) a wheelchair and calculate the time from randomization to wheelchair use or censoring. The endpoint will be analyzed as described for the primary analysis.IVTime spent in disease stage. Based on of the King’s, ALS Milano-Torino and Utrecht staging systems we will calculate the mean time spend in each stage during follow-up. The mean time will be compared between treatment arms.VChange from baseline in Urinary P75^EDC^. The change from baseline in Urinary P75^EDC^ will be analyzed using a mixed effects model as described under II.VIChange from baseline in Neurofilament light and heavy chain. The change from baseline in Neurofilament light chain will be analyzed using a mixed effects model as described under II.

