#### Secondary outcomes

Combined effect on daily functioning and overall survival based on a joint model of survival and ALSFRS-R total scores.Daily functioning, defined as mean change from baseline in ALSFRS-R total score. Disease progression will be monitored using the ALSFRS-R, which is a validated 12-item questionnaire designed to evaluate the functioning of respiratory, bulbar, fine and gross motor function in ALS patients [22]. The total score ranges from 48 (no limitation in daily activities) to 0 (total inability). The ALSFRS-R slope, the difference in scores standardized for time, is often used as measure of disease progression in clinical trials and is significantly associated with survival [23].Respiratory function, defined as mean change from baseline in Slow Vital Capacity (SVC). The SVC is associated with survival in ALS patients [24]. The obtained estimates of the vital capacity will be recorded in liters and standardized using the GLI-2012 reference standard [25].Change in outcome of Plasma creatinine. Plasma creatinine is a part of the safety tests and will be used as one of the secondary endpoints to monitor disease progression [26]. Plasma creatinine is well correlated with functional decline, muscle strength and is highly predictive for overall survival. Due to the effect of disease progression on plasma creatinine, Cystatin C will be used for monitoring kidney function as safety parameter [27].Clinical disease stage, defined as mean time spent in each stage of the King’s and ALS Milano-Torino staging systems. The King’s staging system is a simple clinical staging system, which defines four stages of ALS. The first three stages are defined by functional involvement of a region: bulbar, upper limbs and lower limbs. The number of regions involved gives the stage. Stage 4 is reached if swallowing (4A) or respiratory (4B) difficulty is severe enough to require intervention. This procedure takes the form of a semi-structured interview. MITOS is a similar clinical staging system, in which the stages are defined as loss of independence on the four domains of the ALSFRS-R: swallowing, walking/self-care, communicating and breathing [28]. Studies have shown that both King’s staging and the ALS-MITOS correlate with survival [29, 30].Safety based on the safety assessments including neurological examinations, clinical laboratory evaluations, vital signs and frequency of adverse events (AEs) or serious adverse events (SAEs). (S)AEs will be categorized according to the Common Terminology Criteria for Adverse Events and will be rated for severity and association with study drug.Tolerability defined as time-to-discontinuation of assigned treatment since randomization.Change from baseline in urinary P75^ECD^. P75 is a neutrotrophin receptor that is expressed after motor neural damage and excreted through the urine [31]. Hence, presence of P75^ECD^ in the urine is indicative for the degeneration of motor neurons. P75^ECD^ has been shown to increase over time in patients with ALS and correlates well with measures of functional decline. Moreover, the marker is associated as independent predictor of survival. Therefore, P75^ECD^ may have the utility as a potential pharmacodynamic biomarker and slowing of a rising urine level may be indicative of a biological effect.Change from baseline in plasma Neurofilament light and heavy chain. Neurofilament light and heavy chains in ALS are well known to be correlated with prognosis and remain relatively stable over time [32]. A change in the expression of neurofilament light and/or heavy chain may, therefore, be considered as supporting evidence of disease amelioration in ALS.Neuropsychological status, defined as change from baseline on the ECAS and ALS-FTD-Q. Approximately 35% of the patients, with ALS, experience cognitive or behavioral impairment. The cognitive and behavioral impairment may increase as disease progresses [33]. The neuropsychological status of patients will be evaluated using the Edinburgh Cognitive and Behavioral ALS Screen (ECAS) [34]. The ECAS is independent of motor disability and evaluates five cognitive domains: language functions, executive functions, and letter fluency, memory and visuospatial functioning. If available, ECAS version A and B will be alternated to prevent a training effect in patients. The questionnaire has a behavior screen with a carer interview, this part will not be performed in this study. In addition, we will evaluate behavioral disturbances using the ALS frontotemporal dementia questionnaire (ALS-FTD-Q) [35]. The ALS-FTD-Q is a validated instrument for the screening of behavioral disturbances in ALS. The ALS-FTD-Q has 25 items (including three cognitive items: memory, concentration, and orientation in time), with a 4-point rating scale; the maximum score is 100. A higher score indicates more behavioral disturbances.Global quality of life (QoL), defined as change from baseline on the visual analog scale (single-item scale) and EQ-5D. QoL will be measured using a visual analog scale (single-item scale): a horizontal line of 100 mm ranging from 0 (worst imaginable QoL) to 100 (perfect QoL) [36]. Generic QoL will be measured using the EQ-5D. The EQ-5D measures the health status in terms of five dimensions: mobility, self-care, usual activities, pain and depression. From the EQ-5D a quality-adjust life year (QALY) can be calculated, which is required for cost-utility analysis if a drug is beneficial for patients with ALS [37]. If a patient deceases during the follow-up period, the date will be recorded. If a patient reaches the criteria for respiratory insufficiency (tracheostomy or the use of non-invasive ventilation for ≥22 h per day for ≥10 consecutive days), the date this criterion was met will be recorded and the patient will no longer be part of the study. The time point for all secondary outcomes is month 24.

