#### Sample size {14}

The sample size calculation for this event-driven trial is based on the primary efficacy end point death of any cause or respiratory insufficiency. The trial continues until the required number of events is reached or until 24 months after the last enrolled patient, whichever comes first. In the meta-analysis of lithium carbonate among patients homozygous for the C-allele at SNP rs12608932 in *UNC13A*, we found a crude hazard ratio (HR) of 0.43 and an adjusted HR of 0.30 (active vs. placebo) [8]. Due to the relatively small sample size of the meta-analysis (*n* = 46), we assumed a conservative hazard ratio of 0.50. With the use of a one-sided test at the 0.0250 significance level, the trial would have 80% power if it continued until 72 events occurred in the combined trial groups. We specified one pre-specified stopping rule for efficacy based on the Lan- DeMets procedure with O’Brien-Fleming alpha-spending function when 41 events occur (non-binding).

We used a simulation-based approach to estimate the event probability during follow-up and the required sample size. We assumed that 14.21% of the patients will be homozygous for the C-allele at SNP rs12608932 in *UNC13A*. With a planned maximum enrolment rate of 5–6 patients per month, enrolment of 171 patients (114 on active treatment and 57 on placebo) resulted in 72 events within 48 months since first enrolled patient for 99.5% of our simulated trials.

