#### Statistical methods for primary outcome

The primary endpoint of this study is a composite of time to death from any cause or respiratory insufficiency (DRI; defined as tracheostomy or the use of non-invasive ventilation for ≥22 h per day for ≥10 consecutive days). For each individual we will calculate the primary endpoint as [date of event/censor – date of randomization]/365.25. An indicator variable will be defined specifying whether the patient was alive or had an event at the end of the study. To test the difference between treatment arms, we will use a likelihood ratio test stratified for the randomization factor “*trial site*” and adjusted for “*TRICALS Risk Profile*” as continuous variable. The TRICALS Risk Profile will be fitted as linear effect. This likelihood ratio test will also be used for sequential monitoring of efficacy during one pre-specified interim analysis. The Kaplan-Meier plots estimating the cumulative event rate will be provided for each treatment group. In case of non-proportional hazards, we will estimate the mean difference in Restricted Mean Survival Time (RMST).

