#### Statistical methods for secondary outcomes

ICombined assessment of daily functioning and survival, defined as death from any cause [50, 51]. A joint model will be constructed between a survival model and a longitudinal model for ALSFRS-R data to evaluate the combined effect on both endpoints simultaneously; the full testing procedure is described elsewhere [52]. In short, the survival sub-model will contain treatment allocation as covariate and will be stratified for randomization factors “trial site and adjusted for “TRICALS Risk Profile” as a continuous variable, where the baseline hazard function follows a Weibull distribution [53]. A mixed effects sub-model will be fitted for the ALSFRS-R data with a random intercept and random slope for time per individual. The fixed effects part contains: baseline ALSFRS-R, treatment, time, baseline ALSFRS-R*time and treatment*time. Time will be fitted both linearly as well as non-linearly using restricted cubic splines. The non-linear effect of time will be kept in the model only if significant. If not, fixed non-linear time will be deleted first, followed by random non-linear time. An unstructured covariance matrix will be used to model the correlations among repeated measures. A likelihood ratio test will be used to compare a joint model with the treatment terms vs. a joint model without the treatment terms, thereby estimating the combined effect on both the ALSFRS-R and mortality, irrespective of their association.IIALSFRS-R scores will be analyzed using the same joint model framework outlined above to account for the informative censoring due to patient death (i.e., mortality-adjusted progression). Here, we will use a likelihood ratio test to evaluate the time*treatment interaction from the ALSFRS-R sub-model. A similar strategy will be applied for change from baseline in Predicted %SVC, plasma creatinine, and QoL.

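### Time to wheelchair is plotted by Kaplan-Meier with death and respiratory insufficiency censored, so the curves overstate the share of patients who reach a wheelchair before those events

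*Protocol article*

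**What the plan says.** All references are to the protocol article.

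- **Efficacy: other study parameters, item III.** For each patient, "we will define an indicator variable whether the patient uses (or has a recommendation for) a wheelchair". The analyst will then "calculate the time from randomization to wheelchair use or censoring. The endpoint will be analyzed as described for the primary analysis". Only two outcomes are named, and death is not part of the event.
- **Statistical methods for primary outcome.** This is the method that item III borrows: "we will use a likelihood ratio test stratified for the randomization factor" of trial site and adjusted for the TRICALS risk profile. It adds: "The Kaplan-Meier plots estimating the cumulative event rate will be provided for each treatment group". If hazards are non-proportional, a difference in restricted mean survival time (RMST) is estimated.
- **Secondary outcomes.** When a patient meets the criterion for respiratory insufficiency, "the date this criterion was met will be recorded and the patient will no longer be part of the study".
- **Statistical methods for secondary outcomes.** For ALSFRS-R the plan recognises that death censors informatively and uses a joint model. It extends a similar strategy to vital capacity, creatinine and quality of life. Item III points to the primary analysis instead.
- **General methods.** Secondary endpoints are exploratory and are reported with 95% confidence intervals, without inferential statements.

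**The concern.** The borrowed method suits the primary endpoint because death and RI are themselves the event. One minus Kaplan-Meier is then the proportion of patients with an event.

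For wheelchair, death makes the event impossible and RI ends observation, yet both can only enter as censoring. One minus Kaplan-Meier then estimates how many patients would reach a wheelchair if nobody died or reached RI. That is not a cumulative event rate in the patients studied.

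The gap grows with the rate of death/RI. If lithium prolongs survival, as the trial hypothesises, the gap is larger on placebo. The percentages read off the curves would be too high in both arms, and the distance between the curves would not be the difference in the proportion of patients reaching a wheelchair.

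**Working it through.** **Design figures.** The sample size section says "we assumed a conservative hazard ratio of 0.50" and "With the use of a one-sided test at the 0.0250 significance level, the trial would have 80% power if it continued until 72 events". By Schoenfeld's formula with 2:1 allocation, events = (1.960 + 0.842)² / [(ln 0.5)² × (2/3) × (1/3)] = 73.5, so 74 against the stated 72. Power at 72 events is 79.2%. The stated figure is reproduced closely enough to use the hazard ratio of 0.50 and the 114:57 split. The document states no figure for the wheelchair endpoint itself.

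**Assumptions not in the document**

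- Constant, independent hazards: w for wheelchair and d for death/RI.
- Placebo median time to death/RI of 17.7, 24 or 30 months. The 17.7 is the average survival after diagnosis given in the background section, borrowed here as a median from randomization.
- Net wheelchair risk at 12 months of 20%, 35% or 50%.
- No lithium effect on the wheelchair hazard.

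**Formulas at time T**

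- One minus Kaplan-Meier: 1 − exp(−wT)
- Cumulative incidence of wheelchair before death/RI: w/(w+d) × [1 − exp(−(w+d)T)]
- Death/RI before wheelchair: d/(w+d) × [1 − exp(−(w+d)T)]

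**Mid case** (median 24 months, 35%, T = 18). w = −ln(0.65)/12 = 0.0359 per month. d = ln 2/24 = 0.0289 on placebo and half that, 0.0144, on lithium.

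| | Placebo | Lithium |
|---|---|---|
| 1 − Kaplan-Meier | 47.6% | 47.6% |
| Cumulative incidence | 0.554 × 0.688 = 38.1% | 0.713 × 0.596 = 42.5% |
| Overstatement | 9.4 points | 5.1 points |
| Death/RI before wheelchair | 0.446 × 0.688 = 30.7% | 0.287 × 0.596 = 17.1% |

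The two Kaplan-Meier curves coincide, while incidence is about 4.3 points higher on lithium because more patients live long enough to need a wheelchair. Death/RI comes before wheelchair in (30.7 + 2 × 17.1)/3 = 22% of patients overall.

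**Range at 18 months.** The smallest excess (30 months, 20%) is 4.9 points on placebo and 2.6 on lithium. The largest (17.7 months, 50%) is 15.5 and 8.5. At 12 months the mid case gives 35.0% against 29.9% on placebo and 32.3% on lithium, an excess of 5.1 and 2.7 points.

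**Against sampling error.** Trials of 114:57 patients were simulated with accrual over 31 months, a 24-month cap and stopping at the 72nd death/RI. In the mid case the overstatement is about 1.2 standard errors on placebo and 1.0 on lithium. The implied standard errors are about 9.4/1.2 = 7.8 and 5.1/1.0 = 5.1 points, so the arm difference has a standard error of about √(7.8² + 5.1²) = 9.3. The 4.3-point distortion is therefore 4.3/9.3 = 0.46 standard errors. Coarser rounding of the same figures gives about 0.4.

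**Dependence between the events.** With a shared log-normal frailty (log-SD 0.7, mean one), the mid-case overstatement falls to about 0.9 standard errors on placebo and 0.8 on lithium.

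**Direction.** At 24 months, 42 settings were tried: placebo 1 − Kaplan-Meier of 20% to 95%, wheelchair hazard ratios of 1.0, 0.75 and 0.5, and two death/RI hazards. Kaplan-Meier was too high in both arms, and by more on placebo, in every one.

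**The case against.** **The censoring rule is inferred.** Item III does not list reasons for censoring, and a full analysis plan could refine them. That is true. But with a wheelchair-only indicator and two named outcomes, a patient who dies first has nowhere else to go, and the method is fixed by the cross-reference.

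**The comparison of arms is sound.** A reader might infer that the wheelchair test is invalid. It is not. With death/RI censored, the stratified, adjusted likelihood ratio test is a legitimate test of the cause-specific wheelchair hazard. In the no-effect scenario, coinciding Kaplan-Meier curves answer that question correctly. Cumulative incidence shown alone could make longer survival on lithium look like harm. This objection stands. It confines the point to the absolute curves and any RMST drawn from them, and it is why the incidence of death/RI should be shown alongside.

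**The competing risk is smaller than the event count suggests.** A reader might take the planned 72 events in 171 patients (42%) as the competing risk. That count includes deaths and RI after wheelchair use, which do not compete. The mid case gives about 22%.

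**RI does not rule out wheelchair use.** It only ends observation. This also stands, so the quantity corrected here must be worded as wheelchair before death or RI.

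**The endpoint is minor.** It is listed among other study parameters and does not appear in the objectives or the listed outcomes. This stands and sets the severity.

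**Conclusion.** The point holds for the descriptive curves only. As item III is written, the Kaplan-Meier cumulative event rate, and any RMST from it, overstates the share of patients who reach a wheelchair before death/RI. At 18 months the excess is about 5 to 15 points on placebo and 3 to 9 on lithium. In the mid case the arm difference is distorted by about 4 points, which is under half a standard error.

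These sizes rest on assumed wheelchair rates, a borrowed survival figure, constant independent hazards and the design hazard ratio of 0.50. Shared frailty makes them smaller, and so does an earlier time point. The direction, and the larger excess on placebo, held in every setting tried with that hazard ratio.

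The documents do not support a claim that the wheelchair test is wrong, or that the primary result, the stopping rules or the sample size are affected. Severity is minor.

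**What to change.** In item III:

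1. Define the estimand as wheelchair use or recommendation before death or respiratory insufficiency, and name those two as competing events.
2. Replace the Kaplan-Meier plot with Aalen-Johansen cumulative incidence by arm. Show the incidence of death/RI before wheelchair beside it, so that longer survival is not mistaken for harm.
3. Keep the stratified, adjusted model and label its result a cause-specific hazard ratio.
4. Do not take an RMST from the wheelchair Kaplan-Meier curve.

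The cost is a few sentences and a few lines of code. Dates of death and RI are already recorded, and wheelchair use is collected at each quarterly visit. The reported wheelchair percentages will be lower than Kaplan-Meier would show.

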#### Demography and baseline characteristics

Continuous variables are expressed as mean and standard deviation for normally distributed variables and median and range for non-normally distributed variables. Categorical variables will be presented as number of cases and percentage. Baseline characteristics will be compared between the placebo and intervention arm without significance testing. Demography will be summarized by allocation arm (active *vs.* placebo) and overall. Missing data will not be imputed unless otherwise specified. The following baseline variables will be calculated:Body mass index = weight (kg)/height^2^ (m)SVC _Predicted_ (L) = Predicted using GLI equation (Age, height, ethnicity, sex)Predicted %SVC = [SVC _Observed_ (L)/SVC _Predicted GLI2012_ (L)]*100% [48]Diagnostic delay (months) = [date diagnosis – date symptom onset]/365.25Symptom duration (months) = [date randomization – date symptom onset]/365.25ΔFRS = [ALSFRS-R _Baseline_ – 48]/symptom duration [49]TRICALS risk category: quintiles of the linear predictor based on the model described in Westeneng et al. [19]. Linear predictor is based on age, diagnostic delay, %SVC _Baseline_, ΔFRS, FTD, site of symptom onset, and El Escorial classification (see also {10} Eligibility criteria).Utrecht stage: Based on the ENCALS model, the median survival time from onset is predicted per patient (in months). Utrecht Stage is defined as symptom duration/median predicted survival time. Staging categories are I = 0–0.25; II = 0.25–0.5; III = 0.5–0.75; and IV = >0.75.

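### Mean time in each Utrecht stage is compared between arms, but the stage is defined as a baseline ratio with no stated update, so as written the comparison reflects only length of survival and follow-up

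*Protocol article*

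**What the plan says.** Item IV of Efficacy: other study parameters covers time spent in disease stage. From the King's, "ALS Milano-Torino and Utrecht staging systems we will calculate the mean time spend in each stage during follow-up". It then adds: "The mean time will be compared between treatment arms".

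Demography and baseline characteristics introduces its list with "The following baseline variables will be calculated", and Utrecht stage is on that list. There, "Utrecht Stage is defined as symptom duration/median predicted survival time", and "Staging categories are I = 0–0.25; II = 0.25–0.5; III = 0.5–0.75; and IV = >0.75". In the same list, symptom duration ends at the date of randomisation. The denominator is one ENCALS prediction per patient. On the inputs, the entry for TRICALS risk category says "Linear predictor is based on age, diagnostic delay" and goes on to %SVC with a baseline subscript and ΔFRS, which is calculated from the baseline ALSFRS-R. The note to the eligibility criteria ties this risk profile to the ENCALS model.

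The section on additional analyses uses Utrecht stage, cut at 0.25, as a subgroup factor for the primary endpoint. Secondary outcomes gives clinical disease stage as "defined as mean time spent in each stage of the King’s and ALS Milano-Torino staging systems" and does not name Utrecht.

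**The concern.** A time-in-stage comparison can speak to disease progression only if the stage can respond to the patient's condition after randomisation. King's and Milano-Torino can: they rest on functional involvement or loss of function and are scored during follow-up. Utrecht stage, as defined, is built from quantities known on the day of randomisation. The plan does not say that the prediction is renewed.

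A reader of the results would see three staging systems side by side and take all three as evidence on progression. One of them would repeat, in another form, the survival information that the primary endpoint already gives.

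**Working it through.** The plan gives no figure for this comparison, so there is nothing to reproduce. The check is on the definition, followed by an illustration.

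**Algebra.** Let S be symptom duration at randomisation, P the predicted median survival from onset, and T the time from randomisation to event or end of follow-up. S and P are fixed before treatment starts; only T can differ between arms because of treatment.

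- Reading (a), stage fixed as written: time in stage j equals T if S/P lies in stage j, and 0 otherwise.
- Reading (b), numerator running on with calendar time: for a stage bounded by a and b, time in stage = max(0, min(T, bP − S) − max(aP − S, 0)).

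In both, treatment enters only through T.

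**One patient under (b).** S = 15 months is an assumption. P = 36 months is also an assumption, though it agrees with the average of three years from onset given in the Background. Then S/P = 15/36 = 0.417, which is stage II. Stage III starts at 0.50 × 36 − 15 = 3 months and stage IV at 0.75 × 36 − 15 = 12 months, in either arm. Varying the inputs:

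| S | P | S/P | Stage III from month | Stage IV from month |
|---|---|---|---|---|
| 15 | 30 | 0.50 | 0 | 7.5 |
| 15 | 36 | 0.417 | 3 | 12 |
| 12 | 36 | 0.333 | 6 | 15 |
| 15 | 48 | 0.3125 | 9 | 21 |

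**Group illustration.** The hazard ratio of 0.50 and the 24-month maximum come from the protocol. The rest is assumed: exponential event times, placebo median 12 to 36 months from randomisation, P centred at 30 to 48 months, S centred at 15 months, event times independent of S and P, and 400,000 simulated patients per arm. With placebo median 18 and P centred at 36, the mean months in each stage are:

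| | I | II | III | IV | Total |
|---|---|---|---|---|---|
| (a) placebo | 3.31 | 6.28 | 3.26 | 2.81 | 15.66 |
| (a) active | 4.07 | 7.70 | 4.00 | 3.45 | 19.22 |
| (b) placebo | 0.74 | 3.69 | 4.08 | 7.16 | 15.66 |
| (b) active | 0.79 | 4.20 | 4.95 | 9.27 | 19.22 |

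- Under (a), every stage rises by a factor of about 1.23, which is 19.22/15.66, the ratio of mean follow-up. The factor is equal across stages because event times were drawn independently of stage.
- Under (b), the gains are 0.05, 0.51, 0.87 and 2.11 months, so stage IV takes 2.11/3.56 = 59% of the extra time. Its share of follow-up goes from 45.7% to 48.2%.
- Under (b) with a hazard ratio of 1.0, the arms agree apart from simulation noise (0.74/3.68/4.08/7.15 against 0.74/3.69/4.08/7.17). Any effect on function would leave this unchanged, because function does not enter the formula.
- Over the 12 scenarios at hazard ratio 0.50, stage IV always received the largest gain. It took more than half of the extra time when P was centred at 30 or 36, and about 36% to 39% when P was centred at 48. Its share of follow-up rose by 1.0 to 3.9 percentage points.

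All durations here are in months, the unit the list states. The divisor of 365.25 printed beside symptom duration would give years from dates in days; that is a separate matter.

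**The case against.** The strongest reply is that time in stage during follow-up presupposes a stage that is recalculated. The inputs for doing so are collected: the participant timeline schedules spirometry and ALSFRS-R every three months, and both %SVC and ΔFRS feed the model. With an updated prediction, slower decline would lengthen predicted survival and lower the ratio, so treatment could change the stage. This stands as a possibility, so the documents do not support the flat inference that treatment can never change Utrecht stage. But nothing stated provides for such an update, and the baseline list, the randomisation date and the baseline subscript all point the other way. If updating is intended, the definition has to change.

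A reader might also infer that the output runs backwards, making an effective drug look harmful. The documents do not support that. Under the literal reading, all stages rise together. Under the running clock, mean time rises in all four stages, and only the share in stage IV looks unfavourable, whereas item IV compares means. Extra late-stage time with longer survival can also arise with King's and Milano-Torino, so it is not peculiar to Utrecht.

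Nor is the difference between the two lists of staging systems a contradiction in itself, since item IV may add an output beyond the defined secondary outcome. Finally, General methods makes secondary endpoints exploratory and without inferential statements. That limits the importance of the point but does not make the comparison informative.

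**Conclusion.** The point holds in conditional form and is minor. As Utrecht stage is defined, and unless the prediction is updated after randomisation, the planned comparison carries no information on slowing of disease beyond survival and follow-up length. This follows from the definition alone and needs no assumption about event rates.

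The sizes quoted do rest on assumed distributions. What was stable over the scenarios tried is the direction under a running clock: the largest part of the extra survival time falls in stage IV. The use of Utrecht stage as a baseline descriptor and subgroup factor is not touched by this point.

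**What to change.** Either of two changes resolves it.

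1. Delete Utrecht from item IV, so that it names the same two systems as Secondary outcomes, and keep Utrecht stage for baseline description and the subgroup analysis. The cost is one word and the loss of one uninformative output.
2. If Utrecht stage is to remain an outcome, amend its definition in Demography and baseline characteristics so that the stage is re-predicted at each visit from current ALSFRS-R and %SVC. Keep the baseline value under a separate name for the subgroup analysis. The cost is a longer definition and some programming; both measures are already scheduled at every quarterly visit.

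Neither change affects the sample size, the event count or alpha.

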### Objectives {7}

The primary objective of this study is to assess the efficacy of lithium carbonate versus placebo on the composite endpoint of respiratory support free survival, defined as death from any cause or respiratory insufficiency in patients with ALS.

Secondary objectives of this study include the effect of lithium carbonate versus placebo on a combined assessment of mortality and measures of daily functioning, the revised Amyotrophic Lateral Sclerosis Functional Rating Scale (ALSFRS-R), respiratory function, plasma creatinine, and the time to reach advanced disease stages. Further secondary objectives are to evaluate the safety and tolerability of lithium administered orally to patients with ALS, and to assess the effect of lithium carbonate versus placebo on change in urinary P75^ECD^, in plasma neurofilament light and heavy chain, on cognitive functioning and on quality of life.

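### The objective is time to reach advanced disease stages, but the planned outcome is mean time spent in each stage, which for a late stage read alone has no fixed direction of benefit

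*Protocol article*

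**What the plan says.** Objectives {7} names, among the effects to be estimated, those on "respiratory function, plasma creatinine, and the time to reach advanced disease stages". It does not say which stages count as advanced.

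Secondary outcomes words the matching outcome differently: "Clinical disease stage, defined as mean time spent in each stage" of the King's and ALS Milano-Torino (ALS-MITOS) systems. Efficacy: other study parameters, item IV, fixes the analysis: "we will calculate the mean time spend in each stage during follow-up. The mean time will be compared between treatment arms". Item III, just above it, treats wheelchair use as time from randomisation to event or censoring and analyses it like the primary endpoint.

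Three further statements bear on how long a stage can be observed:

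- Secondary outcomes: "The time point for all secondary outcomes is month 24".
- Sample size {14}: "The trial continues until the required number of events is reached or until 24 months after the last enrolled patient, whichever comes first".
- Secondary outcomes, on reaching respiratory insufficiency: "the date this criterion was met will be recorded and the patient will no longer be part of the study".

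General methods makes all secondary endpoints exploratory, reported with 95% confidence intervals and without inferential statements.

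**The concern.** Time to reach a stage and time spent in it are different quantities. The first has a clear direction: later is better. The second does not for a late stage. A drug that delays entry leaves fewer months to be spent there, and a drug that keeps patients alive after entry adds months. The two effects oppose each other, so less, equal or more time in an advanced stage can all be produced by a drug that works.

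The advanced stages are the ones the objective asks about. The estimates will be reported with confidence intervals. A reader who sees a difference near zero, or longer time in stage 4 on lithium, has no rule in the protocol for telling benefit from harm.

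**Working it through.** **1. Wording side by side.** The objective is time to reach advanced stages. The outcome and the analysis are mean time in each stage during follow-up. The article contains no analysis of the first quantity.

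**2. Figures in the plan.** The protocol gives no figure for the stage outcome. The design figure used below is the stop at 72 events. The Schoenfeld formula with HR 0.50, one-sided 0.025, 80% power and 2:1 allocation gives (1.960 + 0.842)² / [(2/9)(ln 0.5)²] = 73.5, so 74 events. At 72 events power is 79.2%. The plan's figure is reproduced closely enough.

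**3. Two-stage calculation.** Assumed monthly placebo hazards, not in the protocol: early to advanced λ = 1/8 = 0.125; early directly to death or respiratory insufficiency d = 0.012; advanced to death or respiratory insufficiency b = 1/10 = 0.10. Put a = λ + d and R(h,T) = (1 − e^(−hT))/h. With everyone followed to T:

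- mean early-stage time = R(a,T)
- mean late-stage time = [λ/(a − b)] × [R(b,T) − R(a,T)]

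Placebo at T = 24: R(0.137) = 7.03 and R(0.10) = 9.09, so late-stage time = (0.125/0.037) × (9.09 − 7.03) = 6.98 months (unrounded terms used).

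| Drug effect (hazards halved) | Early, 24 mo | Late, 24 mo | Late difference, 24 mo | Late difference, 12 mo |
|---|---|---|---|---|
| λ, d and b | 11.78 vs 7.03 | 7.43 vs 6.98 | +0.45 | −0.87 |
| λ only (delay) | 11.18 vs 7.03 | 5.11 vs 6.98 | −1.87 | −1.40 |
| b only (survival) | 7.03 vs 7.03 | 9.98 vs 6.98 | +3.00 | +0.79 |

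The sign differs between effective drugs. For the drug that halves everything, it also differs between horizons.

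**4. Four-stage simulation under the trial's design.** Inputs: 114 vs 57 patients, entry at 5.5 per month, 24-month cap, observation ending at death or respiratory insufficiency, stop at 72 events, 1500 trials per scenario. Transition rates and baseline stage mix are assumed, in slow, base and fast sets. Lithium minus placebo:

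- All transitions halved: the rate ratio for reaching stage 4 is 0.45 to 0.47, yet stage 4 time differs by only −0.07 to −0.55 months. In the base set the differences for stages 1 to 4 are +1.01, +1.74, +1.38 and −0.55. The trial-to-trial SD for stage 4 is 1.06 months, and 70% of trials show a negative difference.
- Progression only halved: stage 4 time −1.11 to −1.51.
- Endpoint hazard only halved: stage 4 time +1.38 to +1.81, although the rate of reaching stage 4 is unchanged (ratio 1.01 to 1.03).
- Progression × 0.7 with endpoint hazard × 0.5: stage 4 time +0.28 to +0.77, with a rate ratio of 0.67 to 0.69.

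**5. Role of follow-up.** With no drug effect all stage differences are about 0. With potential follow-up fixed at 24 months (base set, all transitions halved), the differences are +0.99, +1.80, +1.46 and −0.54, almost those of step 4. Observed time still differs by arm, 20.4 vs 16.8 months under the event-driven stop, because death or respiratory insufficiency ends it. In the futility scenario of Interim analyses, 11.3% of patients remain 18 months or more and 1.8% complete 24. A mean taken over follow-up as it occurred then refers to no fixed horizon, and step 3 shows that the horizon matters.

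**The case against.** The strongest reply is that every stage is to be reported, not one late stage alone. Early-stage time does carry the signal: in step 3 it is 11.78 vs 7.03 months when all hazards are halved. In step 4 the summed time in stages 1 to 3, which is restricted time to stage 4 or death/respiratory insufficiency, favours the drug by +3.2 to +4.1 months. This stands. A reader might infer that the whole comparison can reverse or cannot inform the objective; the plan and the calculations do not support that.

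A reader might also blame staggered entry and the event-driven stop. Randomisation balances these, and step 5 shows no difference under no effect. They leave the horizon undefined but do not by themselves favour an arm.

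Nor is the gain in early-stage time shown to be biased downward. A simulation of the two-stage model with the event-driven stop gave 3.66 months against 4.78 over a full 24 months, about 23% less. That is a shorter horizon at work: the formula gives 10.34 − 6.68 = 3.66 at a fixed 18 months, and only 8.18 − 5.89 = 2.29 at 12.

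That censoring is ignored cannot be concluded either. Item IV is two sentences in a condensed article, and the estimator may be set out in the full protocol or analysis plan.

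Finally, the outcome is exploratory, and the joint model of ALSFRS-R and survival already addresses progression with death taken into account. That limits the weight of the point but does not remove the mismatch.

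**Conclusion.** The point holds as a mismatch between the objective and the outcome meant to serve it. Followed as written, the plan does not directly estimate time to an advanced stage. The late-stage means it will report can be lower, similar or higher for an effective drug: −1.87 to +3.00 months in the two-stage calculation at 24 months, and −1.51 to +1.81 in the four-stage scenarios listed. The cause is the measure itself, together with death or respiratory insufficiency ending observation. The event-driven stop adds that the mean depends on whatever follow-up occurred, not on the month-24 time point.

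The sizes rest on assumed transition rates and are illustrative. The opposing directions follow from the definition, but near-exact cancellation is one case among several. The primary analysis, sample size and stopping rules are unaffected. The point deserves correction as an interpretability problem in an exploratory outcome, and no more than that.

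**What to change.** In Secondary outcomes and in item IV, add time from randomisation to first King's stage 4 or death/respiratory insufficiency, among patients below stage 4 at baseline. Add the same for an ALS-MITOS stage named in advance as advanced. Analyse both as item III is analysed.

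If time in stage is kept, report it as restricted mean time in stage to one common stated horizon, with censoring handled, and state for each stage which direction is benefit. Align the wording of Objectives {7} with what is analysed.

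The cost is mainly wording. King's stage and ALSFRS-R are scheduled at baseline and quarterly, and gastrostomy and ventilation are recorded. There are three drawbacks:

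- Patients already in the advanced stage at baseline drop out of the time-to-stage outcome. Some may enrol, since only ventilation of 22 hours or more per day or tracheostomy is excluded. Their number is not given.
- The composite overlaps with the primary endpoint.
- The minimum data for remotely followed patients include ALSFRS-R but not King's staging, so stage 4 would have to be taken from the recorded interventions for them.
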